## METHODS

### Overview

The ELECT-TDCS trial randomizes patients into: sham-tDCS/placebo-pill (placebo group), sham-tDCS/escitalopram (escitalopram group) and active-tDCS/placebo-pill (tDCS group). It was approved by the Local and National Ethics Committee (CAAE:10173712.3.0000.0076) of the University Hospital and Clinics Hospital of the University of São Paulo and is registered in clinicaltrials.gov (NCT01894815). All study participants provide written, informed consent for participation in the study.

Our null hypothesis is that the improvement, i.e. the difference in efficacy between baseline and endpoint measurements of the tDCS group (µ_tDCS_) will be less than or equal to 50% (retention fraction *f* ≤ 50%) of the difference in the improvement between escitalopram and placebo (µ_drug_ - µ_placebo_). The study’s primary aim is to prove the alternative hypothesis, i.e. that this difference is greater than 50% (*f* > 50%).

$$H_{o}:\;{µ}_{tDCS}\;-\;{µ}_{placebo}\;\leq \;50\%\;({µ}_{drug}\;-\;{µ}_{placebo})$$

*or*

$$H_{o}:\;{µ}_{tDCS}\;-\;0.5\;{µ}_{placebo}\;-\;0.5\;{µ}_{drug}\;\leq \;0$$

$$H_{A}:\;{µ}_{tDCS}\;-\;{µ}_{placebo}>\;50\%\;({µ}_{drug}\;-\;{µ}_{placebo})$$

*or*

$$H_{A}:\;{µ}_{tDCS}\;-\;0.5\;{µ}_{placebo}\;-\;0.5\;{µ}_{drug}>\;0$$

In a non-inferiority triple-arm trial, there are three relevant comparisons: (1) experimental treatment versus active comparator (i.e. tDCS versus escitalopram); (2) experimental treatment versus placebo; and (3) active comparator versus placebo. Authors such as Koch and Röhmel^29^ have considered that the third comparison is not strictly necessary if the former two were significant, but in their approach, two or three null hypotheses would have to be independently rejected (thereby decreasing the P value), or the trial would only be valid if all hypotheses were rejected.^30^ Therefore, we use here an alternative model presented by Pigeot et al.^31^ and already used in the literature,^32^ in which the study aim can be presented in a single H_0_, which simultaneously tests the non-inferiority between active treatments and their superiority against placebo, thereby decreasing the number of multiple comparisons.

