Our secondary aims are to explore the clinical improvement in terms of response status (more than 50% of improvement from baseline to endpoint) and remission status (HDRS-17 ≤ 7 at endpoint). We will also explore improvement in depression using the MADRS and the BDI. Finally, we will also investigate whether any early improvement (week 3) was observed between the groups.

We also aim to identify several predictors and mediators of tDCS response, as described below.

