### Statistical analysis

In accordance with the recommendations of Pigeot et al.^31^ and Rothmann et al.,^79^ we use a modified *t* test to address our primary study hypothesis (i.e. that tDCS is non-inferior to escitalopram). A *t* test involves obtaining a T value, which should be higher than (in a one-tailed test, as in our study) or different to (in a two-tailed test) a critical *t* value. The T value is obtained by dividing the difference in the means by the mean error (obtained according to the variance and sample size). For this analysis, the T value will be obtained as follows:

$$T=({µ}_{tDCS}-0.5{µ}_{PLACEBO}-0.5{µ}_{DRUG})/\sigma \surd (1/n_{TDCS}+0.25/n_{DRUG}+0.25/n_{PLACEBO})$$

or

$$T=7.44({µ}_{tDCS}-0.5{µ}_{PLACEBO}-0.5{µ}_{DRUG})/\sigma (considering\;that\;the\;n\;values\;are\;known)$$

This T value should be higher than the critical *t*, which for a one tailed α of 0.025 and 237 (N-3) degrees of freedom would be 1.97.

We will also perform exploratory analyses to identify whether a significant difference between the groups is observed over time. Therefore, we will perform mixed-model analyses of variance (ANOVAs) with one independent, within-subject variable (time, with three levels: baseline, week 3 and endpoint) and one independent, between-subject variable (group, with three levels). The dependent variables will be the scores from HDRS, MADRS or BDI. To determine whether a statistical significance is observed at a two-tailed p value of 0.05 or less, post-hoc analyses will be performed to analyze the main and interaction effects of our interventions. Exploratory analyses will also be performed to identify the influence of clinical, demographic and biological variables on the outcome. In addition, logistic regressions will be performed using response or remission as dependent variables and the group as an independent variable. Adverse effects will be assessed by counting the number of events in each group at each evaluation time. The chi-square test will be used to compare the frequency of adverse effects between the treatment groups.

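### The exploratory group-by-time ANOVA counts the pre-treatment baseline as an outcome visit, so its group main effect is two thirds of the post-baseline difference and should not be read as a treatment effect; baseline-adjusted contrasts at week 3 and endpoint would serve better

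*Protocol article*

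**What the plan says.** The Statistical analysis section of the protocol article introduces these models as exploratory: "We will also perform exploratory analyses to identify whether a significant difference between the groups is observed over time". The within-subject factor is "time, with three levels: baseline, week 3 and endpoint", and the between-subject factor is the three treatment groups. On the outcome it says: "The dependent variables will be the scores from HDRS, MADRS or BDI". These are raw scores, not changes from baseline. At a two-sided 5% level, "post-hoc analyses will be performed to analyze the main and interaction effects of our interventions".

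Two other statements set the context:
- The secondary aims in the Overview of the Methods include "whether any early improvement (week 3) was observed between the groups", and improvement on MADRS and BDI.
- The primary hypothesis is handled separately: "we use a modified *t* test to address our primary study hypothesis". Its quantity is a change score, "the difference in efficacy between baseline and endpoint measurements of the tDCS group".

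The ANOVA is the only model the article states for continuous MADRS and BDI scores and for HDRS over time.

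**The concern.** Baseline is measured before treatment. When it is a level of the outcome's time factor, the group main effect averages one visit that cannot carry a treatment effect with two that can. The plan names main effects among the things to be analysed, lists them beside the interaction, and does not say which is the test of interest. A null main effect could then be taken as evidence of no group difference on a scale where a real difference exists after baseline.

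The interaction avoids this dilution but has two weaknesses. It is one omnibus test over three groups and three times, so a significant result does not say which arm or visit differs, although the week-3 aim concerns one visit. Its component contrasts subtract the whole baseline score, which is less precise than adjusting for baseline.

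At stake are the week-3 aim and the secondary scales, not the non-inferiority conclusion.

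**Working it through.** There is no figure in the plan to reproduce on this point. The dilution is algebra; the power figures are illustrative.

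**1. What the group main effect estimates.** Let d0, d3 and d10 be a pairwise group difference at baseline, week 3 and endpoint.
- Main effect with baseline as a level: (d0 + d3 + d10)/3. Under randomisation E[d0] = 0, so this is (d3 + d10)/3.
- Average post-baseline difference: (d3 + d10)/2.
- Ratio: (1/3)/(1/2) = 2/3, whatever d3 and d10 are.
- Against the endpoint difference, with d3 = g × d10, the ratio is (1 + g)/3: 33%, 50% and 67% for g = 0, 0.5 and 1.

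**2. What the interaction tests.** Its contrasts are d3 − d0 and d10 − d0, the differences in change from baseline. Their expectations are d3 and d10, so there is no dilution. With three groups and three times it has (3 − 1)(3 − 1) = 4 degrees of freedom.

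**3. Power inputs.** From the article: 90 v 60 patients for an active arm against placebo, and two-sided 5%. Assumed: equal SD (set to 1) at each visit, one correlation ρ between all visits, endpoint effect d = 0.5 SD, week-3 fraction g, no dropout, 237 df.
- Standard-error factor: √(1/90 + 1/60) = 0.1667.
- SD of the three-visit mean: √((1 + 2ρ)/3).
- SD of a change score: √(2(1 − ρ)).
- SD of a baseline-adjusted score: √(1 − ρ²).

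**4. Base case, ρ = 0.5 and g = 0.5.**

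| Contrast | Effect / (SD × 0.1667) | Noncentrality | Power |
|---|---|---|---|
| Group main effect | 0.25 / (0.816 × 0.1667) | 1.84 | 45% |
| Endpoint, change score | 0.5 / (1.000 × 0.1667) | 3.00 | 85% |
| Endpoint, baseline-adjusted | 0.5 / (0.866 × 0.1667) | 3.46 | 93% |
| Week 3, change score | 0.25 / (1.000 × 0.1667) | 1.50 | 32% |
| Week 3, baseline-adjusted | 0.25 / (0.866 × 0.1667) | 1.73 | 41% |

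The unadjusted endpoint difference (SD 1) also has 85%; at ρ = 0.5 it coincides with the change score.

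**5. The 4-df interaction in the same case.** Take both active arms as equally effective. The noncentrality is (180 × 60/240) × vᵀV⁻¹v, with v = (0.25, 0.5) and V having 2(1 − ρ) = 1 on the diagonal and 1 − ρ = 0.5 off it. Then vᵀV⁻¹v = (0.0625 − 0.125 + 0.25)/0.75 = 0.25, the noncentrality is 45 × 0.25 = 11.25, and power is about 77%.

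**6. Lower correlation, ρ = 0.3.** Endpoint change score: 0.5/(1.183 × 0.1667) = 2.54, power 71%. Baseline-adjusted: 0.5/(0.954 × 0.1667) = 3.14, power 88%.

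**7. Range over ρ and g in {0.3, 0.5, 0.7}.** Main effect 30–64%; 4-df interaction 60–96%; endpoint change score 71–97%; endpoint baseline-adjusted 88–99%.

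**8. With the article's ε of 1.5.** Using it as the SD at each visit (a further assumption) gives d = 1/1.5 = 0.67 SD. Over the same grid the main effect has 49–87% power and the adjusted endpoint contrast about 99% or more. At ρ = 0.5 and g = 0.5 the main effect has about 68% and the 4-df interaction about 96%.

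**The case against.** The strongest reply is that the plan does not rely on the main effect. The interaction is also planned, it answers the stated question of whether groups differ over time, and keeping baseline as a level is a usual way to pose that question. Its contrasts are undiluted and agree in kind with the primary quantity, which is also change from baseline. Its power is adequate under the article's own ε. All of this stands. A reader might infer that the model tests a diluted quantity in place of the week-3 and endpoint differences. The article does not support that, because the interaction and post-hoc analyses can supply both.

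A reader might also infer that the published treatment effect would be about half the endpoint effect. Nothing in the article says that the averaged main effect will be reported as the treatment effect.

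It can further be said that contrasts and covariates belong in an analysis plan, which is not shown, and that the work is exploratory. The exploratory label limits the consequences. The first argument carries less weight here, since the article itself fixes the model, the time levels, the raw-score outcome and the effects to be analysed. Preferring covariate adjustment to change scores is a gain in precision; the change-score contrast is not an error.

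**Conclusion.** The point holds for the group main effect. With baseline as a time level, that effect is 2/3 of the week-3/endpoint average difference, which follows from randomisation alone, and it should not be interpreted as a treatment effect.

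The interaction is valid and undiluted, but it names neither visit nor arm, and its change-score contrasts give away some precision. Endpoint power is 85% v 93% with adjustment at correlation 0.5, and 71% v 88% at 0.3. Those figures rest on an assumed endpoint effect of 0.5 SD, equal SDs and correlations across visits, 90 v 60 patients and no dropout. The gap narrows as the correlation or the effect rises.

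The modified t test for non-inferiority, its alpha and the sample size are not touched. This is a worthwhile low-cost improvement to exploratory and secondary analyses, and it does not threaten the trial's main conclusion.

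**What to change.** Take baseline out of the outcome's time factor. For each of HDRS, MADRS and BDI, fit a repeated-measures model to the week-3 and endpoint scores with group, visit, group-by-visit and that scale's own baseline as covariate. Name the pairwise group differences at week 3, which is the early-improvement aim, and at endpoint as the contrasts to be reported with confidence intervals. State that no group main effect including baseline will be tested or reported as a treatment effect.

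If the three-level ANOVA is kept, the minimum change is to name the interaction and its week-3 and endpoint contrasts as the tests of interest.

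The cost is a few sentences of analysis wording. The baseline scores are already collected, no new data are needed, and standard software fits the model.

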**Table 1. f3:**
[figure not shown]
Study schedule for the ELECT-TDCS

To assess adverse effects, we use the Systematic Assessment for Treatment of Emergent Effects (SAFTEE)^37^ and the tDCS adverse events questionnaire.^10^ We apply the Young Mania Rating Scale (YMRS) to assess hypomanic symptoms, which have already been described after tDCS antidepressant treatment.^38^^,^^39^^,^^40^^,^^41^ Also, we include neuropsychological assessments in our study, primarily to verify that tDCS will not be associated with cognitive impairment, using the Montreal Cognitive Assessment (MOCA), the Wechsler Adult Intelligence Scale-III digit span (forward and backward) and digit symbol coding subtests, the Verbal Fluency Test (FAS and animal/fruit categories) and the Trail Making test. The Temperament and Character Inventory (TCI) is being collected at baseline and endpoint to assess the personality traits associated with and modified by the antidepressant treatment. We also assess blinding performance by asking patients to guess their own treatment allocation group at week 3 and at the endpoint, and ask interviewers to make the same guesses regarding these patients’ treatment.

Furthermore, we are investigating several biomarkers, including:

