According to this formula, for *f* = 0.5, k_p_ is 0.69. Therefore the optimal proportion for allocation between the groups is 1:1:0.69, or approximately 3:3:2, as used in ELECT-TDCS.

We estimated our sample size in accordance with the suggestion of Pigeot et al.^31^ for non-inferiority, triple-arm trials:

$$N_{arm}\geq {\left(t_{1-\alpha ,\;3n-3}\;+\;t_{1-\beta ,\;3n-3}\right)}^{2}*(1+f^{2}+{\left(1-f\right)}^{2})\;{*\left[\left(\sigma /\;{µ}_{DRUG}-{µ}_{PLACEBO})/(r-f\right)\right]}^{2*}$$

This formula shows that the sample size is a product of three factors (in parentheses). The factor in the first parentheses take into account the values of α and β, which were, respectively 0.025 (one-tailed) and 0.2. The factor in the second parentheses is the *f* value (the higher the *f* value is, the larger the necessary sample size will be), which was determined as 0.5 for our study. The factor in the last parentheses involves the standard deviation and effect sizes of the interventions. We took the value of the standard deviation to be a function of the difference in efficacy between the active comparator and the placebo:^31^

$$\sigma =\varepsilon \;({µ}_{DRUG}-{µ}_{PLACEBO})$$

The ε value indicates that the standard deviation is associated with the mean difference values observed in the study. It ranges from 0.2 to 2, and values > 1 are considered conservative. In the present study, we took the ε value to be 1.5, i.e. the standard deviation would be 1.5 times the value of the difference in efficacy between the active intervention and the placebo, which is compatible with depression studies in which the variance is usually high.^†^

Therefore, considering an attrition rate of 13% (similar to SELECT-TDCS), β = 0.2, α_one-tailed_ = 0.025, *f* = 0.5 and ε = 1.5, a total sample of 240 patients will be necessary in order to reject our null hypothesis. For 3:3:2 randomization, this means that in the end, 90, 90 and 60 patients will be respectively allocated to the tDCS, escitalopram and placebo groups.

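### The adverse-effect comparison counts events and does not make the patient the unit of the chi-square test, so the test holds its level only under some readings of the text.

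*Protocol article*

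**What the plan says.** The Statistical analysis section gives adverse effects two sentences. The first sets the counting rule: "Adverse effects will be assessed by counting the number of events in each group at each evaluation time". The second names the test: "The chi-square test will be used to compare the frequency of adverse effects between the treatment groups". Neither mentions patients with an effect, a denominator, or whether counts are taken by type of effect or over all types together.

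The Procedures section names two instruments for adverse effects, SAFTEE and a tDCS adverse events questionnaire. Their item structure is not described. The arms are unequal: "90, 90 and 60 patients will be respectively allocated to the tDCS, escitalopram and placebo groups".

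No significance level is attached to the adverse-effect test. For the exploratory efficacy analyses the section uses 0.05: "statistical significance is observed at a two-tailed p value of 0.05 or less". The evaluation times for adverse effects do not appear in the text, and the schedule table is not shown.

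**The concern.** A Pearson chi-square test takes its variance from the assumption that the units counted are independent. Patients are independent of one another, but effects reported by the same patient generally are not: some patients report many and others none. When events are the unit, this between-patient variation enters the statistic but not its reference distribution, so p-values come out too small.

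Tolerability is a large part of the case for tDCS. The abstract describes it as almost free of adverse effects, and the Discussion returns to this as an advantage over drugs. A test that does not hold its level could let a few patients with many complaints produce an apparent difference between arms, for or against tDCS.

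**Working it through.** The plan attaches no figure to this analysis, so there is nothing to reproduce. The check asks how the stated test behaves when the arms truly do not differ.

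**Inputs**
- From the protocol article: arms of 90, 90 and 60.
- Assumed: alpha 0.05, borrowed from the exploratory analyses.
- Assumed: mean events per patient at one visit of 0.5, 1 or 2, with gamma-Poisson variation between patients. The variance-to-mean ratio is then φ = 1 + mean × (variance of the gamma factor). For example, mean 1 with gamma variance 0.5 gives φ = 1.5, and mean 2 with gamma variance 1 gives φ = 3.

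**Approximation.** Take event totals per arm, with expected totals scaled to arm size. Under no difference, the statistic behaves like φ times a chi-square with 2 degrees of freedom. The 5% critical value is 5.99, so the false-positive rate is about P(χ²₂ > 5.99/φ) = exp(−5.99/(2φ)).

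**Simulation.** 10,000 trials per setting. The Monte Carlo standard error at 5% is √(0.05 × 0.95/10,000), about 0.2 percentage points.

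| φ | exp(−5.99/(2φ)) | Simulated, event totals |
|---|---|---|
| 1 | 5.0% | 5.0–5.1% |
| 1.25 | 9.1% | 8.4% |
| 1.5 | 13.6% | 13.8–13.9% |
| 2 | 22.4% | 21.9–22.2% |
| 3 | 36.8% | 36.5–37.4% |
| 5 | 54.9% | 54.5% |

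In the same simulated trials, a 3×2 chi-square on patients with at least one event rejected in 4.6% to 5.4%, which is nominal throughout.

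**One effect type at one visit.** Each patient now contributes 0 or 1, with prevalence p.
- Tabulated as patients with and without the effect, the test rejected in 4.7% to 5.4%, so there is no inflation.
- If only the counts of affected patients are compared, without the unaffected, then φ = p(1 − p)/p = 1 − p, which is below 1, and the test is conservative. The formula gives 3.6%, 2.4% and 0.7% for p of 0.1, 0.2 and 0.4; simulation gave 3.4%, 2.4% and 0.7%.

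The same sentence in the plan therefore covers a test that rejects too often, one that rejects at its nominal rate and one that rejects too rarely, depending on what is tabulated.

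**The case against.** The strongest reply is that the text does not commit to an event-level test. Frequency of adverse effects can mean the proportion of patients affected, and for one effect type at one visit a with/without table is valid and brings in the arm sizes automatically. This stands in part: the wording is open to that reading. But the sentence before it makes the number of events what is counted, and nothing supplies the patient denominator that the valid reading needs.

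Second, several effects per patient within a visit is an inference. The article names the instruments without describing their items, and it gives no event rates. This also stands. It is why the result is a range that starts at no inflation (φ = 1).

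Third, an article may leave tabulation detail to a fuller document that is not shown. That is fair for matters such as the handling of sparse cells. The counting rule, however, is stated here, and it names events.

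Two stronger readings are tempting and are not supported:
- A reader might infer that repeats of the same effect are pooled across visits. Counting is separate at each evaluation time, so the plan does not do this.
- A reader might infer that the larger arms would produce differences simply by size. That requires equal expected counts in unequal arms, which the plan never states.

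**Conclusion.** The point holds in conditional form and is minor. The plan counts events and does not make the patient the unit of its chi-square test. If several effects per patient are summed within a visit, a nominal 5% test has a false-positive rate of about 8% at φ = 1.25, 14% at 1.5, 22% at 2 and 37% at 3. These figures rest on the assumed dispersion, on a 0.05 level that the plan does not state for this test, and on expected totals scaled to arm size. It does not follow that the planned test is necessarily anticonservative: by effect type and visit it is valid with a with/without table and conservative (0.7% to 3.4%) on counts alone. With patients having at least one effect as the unit, the level is held in every setting examined. Only a secondary safety comparison is affected.

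**What to change.** Replace the counting sentence so that the patient is the unit. At each evaluation time, compare between arms the number of patients with at least one adverse effect, overall and for each effect type, with the patients assessed in that arm at that time as denominator. Use chi-square, or an exact test where cells are sparse. If total events are also to be compared, use a count model that allows overdispersion, such as negative binomial or Poisson regression with robust variance.

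The cost is one or two sentences in the analysis plan, best settled before unblinding. It uses data already collected and changes nothing in the conduct of the trial.

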## INTRODUCTION

Major depressive disorder (MDD) is a psychiatric condition with high prevalence and recurrence worldwide,^1^ and it is projected to be the second greatest cause of disability worldwide in 2020.^2^ However, antidepressant drugs are only moderately effective for MDD treatment.^3^ Moreover, common adverse effects can lead to treatment discontinuation and recrudescence of symptoms.^4^ For these reasons, novel treatment strategies are continuously pursued.

In this context, non-invasive brain stimulation therapies (electroceuticals) have been increasingly investigated as non-pharmacological MDD treatments, such as repetitive transcranial magnetic stimulation (rTMS), a technique that discharges potent electromagnetic fields through a coil placed over the patient’s head.^5^ Repetitive TMS is an effective treatment for MDD,^6^^,^^7^ although issues such as high cost of application, discomfort and specialized technology limit widespread adoption.^8^

Transcranial direct current stimulation (tDCS) is a neuromodulatory technique that presents low cost, high portability and a benign profile of adverse effects and is relatively simple to use.^9^^,^^10^ It consists of applying a low-intensity electric current across the patient’s head using two electrodes on the scalp. In a seminal study in 2000, Nitsche and Paulus demonstrated that anodal and cathodal tDCS applied over the motor cortex respectively increased and decreased motor cortical excitability, as measured by means of TMS motor-evoked potentials,^11^ thereby showing that tDCS could alter cortical excitability.^12^ Its effects depend not only on the polarity of the current, but also on other factors, such as baseline cortical activity, neuronal orientation and delivered current intensity and duration.^13^^,^^14^^,^^15^

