The pharmacological intervention starts simultaneously with tDCS and consists of 10 mg pills of escitalopram oxalate or placebo. Patients receive 10 mg/day of escitalopram/placebo for the first 3 weeks and 20 mg/day for the remaining 7 weeks. Escitalopram was chosen because it is an effective antidepressant treatment with few adverse effects^36^ and its full dose (20 mg/day) is relatively easier to achieve than those of other antidepressant drugs. Thus, maximum dose-up titration can be done in the beginning of the trial. Therefore, we are able to compare tDCS against a full dose of an effective antidepressant without compromising blinding due to adverse effects.

The escitalopram pills are from Libbs (São Paulo, Brazil), a Brazilian pharmaceutical drug company that produces Reconter (escitalopram oxalate), which is a generic drug product comparable to the brand reference Lexapro (Lundbeck Brasil Ltda., Rio de Janeiro, Brazil). In Brazil, all generic drug products have their bioequivalence tested and certified by the Brazilian Health Surveillance Agency (ANVISA). We also independently assessed whether Reconter would be comparable to Lexapro in terms of dosage, strength and quality by testing both drugs in the Clinical Analysis Laboratory of the School of Pharmaceutical Sciences of the University of São Paulo. They achieved the same performance regarding their physical-chemical properties. The School of Pharmaceutical Sciences also produces the placebo pills, which are identical to the Reconter pills in terms of shape, color, weight and taste. Escitalopram and placebo pills are put in identical opaque bottles, identified solely by a number corresponding to the patient’s code. Adherence to the drug intervention will be verified by means of a pill count at the end of the study.

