For non-inferiority trials, it is unclear which approach (intention-to-treat, ITT; or per protocol, PP) should be used. ITT imputes data from study drop-outs and, although conservative for superiority trials, it can favor the hypothesis of lack of difference between groups in a non-inferiority design and, therefore, benefit (instead of penalizing) a non-inferiority design with methodological flaws. Nonetheless, neither the FDA^83^ nor the EMA^84^ clearly recommend the optimal approach and they suggest that both ITT and PP should be used. Mulla et al.^85^ also suggested that ITT should be used because it has the additional benefit of being more robust in relation to bias, compared with PP analysis. Therefore, missing data will be handled using an ITT approach and the findings will be confirmed through PP analysis. Finally, we will perform additional analyses according to the patients’ adherence to the study, using the categories of “fully adherent sample” (patients who missed or rescheduled two visits or fewer) and “completer sample” (patients who completed the study in accordance with the protocol). This approach was also used by George et al.^6^

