## DISCUSSION

ELECT-TDCS will be the largest trial to date assessing the efficacy of tDCS and the first designed to specifically compare the efficacy of tDCS with a full dose of escitalopram. Demonstrating that tDCS presents efficacy similar to that of a pharmacological treatment is important, because antidepressant drugs present several relative and some absolute contraindications against use. Therefore, tDCS could increase the therapeutic arsenal for use among depressed patients who cannot or are not willing to use antidepressant drugs, e.g. pregnant women,^86^ HIV patients^87^ and patients presenting clinical conditions in which the pharmacokinetic interactions are problematic.^88^

Our study is also interesting from a cost-efficacy perspective, since tDCS is an affordable, portable and ease-to-use therapy. The cost of antidepressant therapy consisting of tDCS might, in fact, be comparable to that of antidepressant drugs, if it is taken into consideration that one tDCS device can be used to perform several applications per day and that one operator can deliver tDCS to two to three patients simultaneously. Finally, tDCS is a technique with few adverse effects.^10^ There are at present no reports of seizures or other severe life-threatening events. The most serious adverse effect reported hitherto is skin burn at the application site, and this has been an uncommon finding.^89^

Another key aspect of ELECT-TDCS is that several biomarkers will be assessed in a multimodal approach. tDCS does not seem to induce peripheral effects in cases of depression, such as changes to blood neurotrophic factors.^77^^,^^90^^,^^91^ However, it increases central neuroplasticity as indexed by paired associative stimulation,^92^ modulates cortical activity as indexed by electroencephalography^93^ and improves working memory and affective processing.^94^^,^^95^^,^^96^ Finally, since the same analyses will be performed in the escitalopram group, we will also explore whether the biological predictors and mediators are different between tDCS and escitalopram responders.

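### Adverse effects are counted as events at each evaluation, with no stated denominator and no cumulative per-patient measure, so late counts can understate harm in the arm that loses more patients to adverse effects

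*Protocol article*

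**What the plan says.** The adverse-effect analysis is given in two sentences of the Statistical analysis section: "Adverse effects will be assessed by counting the number of events in each group at each evaluation time", and "The chi-square test will be used to compare the frequency of adverse effects between the treatment groups". No denominator or safety population is named. The text does not say whether the chi-square test is run at each evaluation or on totals. It states neither a per-patient cumulative count nor a count of withdrawals due to adverse effects.

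Related statements elsewhere in the protocol article:

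- Procedures: "To assess adverse effects, we use the Systematic Assessment for Treatment of Emergent Effects (SAFTEE"), together with a tDCS adverse events questionnaire. The visits at which they are given are in Table 1, which is not reproduced in the text at hand.
- Design and sample size determination: the sample size is set "considering an attrition rate of 13% (similar to SELECT-TDCS"). The rate is not split by arm or by reason.
- Introduction, on antidepressant drugs: "common adverse effects can lead to treatment discontinuation and recrudescence of symptoms".
- Interventions: "Patients receive 10 mg/day of escitalopram/placebo for the first 3 weeks and 20 mg/day for the remaining 7 weeks".
- Statistical analysis, closing paragraph: "missing data will be handled using an ITT approach and the findings will be confirmed through PP analysis". This follows a discussion of analysis sets for non-inferiority and is not said to extend to adverse effects.
- Discussion: "tDCS is a technique with few adverse effects". The Results paragraph of the Abstract makes a stronger statement of the same kind.

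**The concern.** A count taken at an evaluation can include only patients who attend it. If patients leave because of an adverse effect, their effect is missing from every later count, and the loss is largest in the arm with the most intolerance. The protocol recognises the mechanism, since its Introduction says that adverse effects of antidepressants lead to discontinuation. The dose schedule adds to it. An effect that first appears after the week-3 step can be picked up only at a later evaluation, and a patient who left because of it may not attend one.

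At stake is the tolerability comparison. The article argues that similar efficacy would matter clinically because tDCS has few adverse effects. A distortion here could go either way. It could hide a real tolerability advantage of tDCS if escitalopram loses more affected patients, or hide tDCS harm if tDCS is the arm that loses them. The ITT rule does not evidently help, because it is set out for the non-inferiority comparison and nothing says that adverse effects are imputed.

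**Working it through.** The plan gives no adverse-effect rate and no power for safety, so there is no figure of its own to reproduce. What follows is an illustration.

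**Inputs from the protocol article:** 90 patients each on escitalopram and tDCS; attrition 13%, taken as 12 of 90 (13.3%) in each arm.

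**Assumed inputs, not in the documents:** the effect truly occurs in 40% on escitalopram (36 of 90) and 25% on tDCS. It persists to the last evaluation in patients who stay. tDCS losses are unrelated to it. Of the 12 escitalopram losses, *a* are due to the effect and the other 12 − *a* are unrelated to it.

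**Rate seen at the last evaluation.** After removing the *a* patients who left because of the effect, the remaining rate is (36 − *a*)/(90 − *a*). The other losses are unrelated, so the 78 who stay show the same rate.

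| *a* | Escitalopram, among 78 present | Excess over 25% |
|---|---|---|
| 0 | 36/90 = 40.0% | 15.0 points |
| 4 | 32/86 = 37.2% | 12.2 points |
| 8 | 28/82 = 34.1% | 9.1 points |
| 12 | 24/78 = 30.8% | 5.8 points |

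**If all 90 randomised form the denominator instead**, multiply each rate by 78/90. tDCS becomes 25% × 78/90 = 21.7%. Escitalopram becomes 32.2%, 29.6% or 26.7% for *a* = 4, 8, 12, so the excess is 10.6, 7.9 or 5.0 points. With *a* = 0 it is 15 × 78/90 = 13.0 points. Late counts fall under either denominator, and the excess is smaller over those randomised.

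**Power**, two-sided 5%, by the normal approximation Φ[(Δ − 1.96·s₀)/s₁], where Δ is the difference in proportions, s₀ its standard error with the pooled proportion and s₁ its standard error with separate proportions:

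- 40% v 25%, 90 v 90: (0.15 − 1.96 × 0.0698)/0.0689 = 0.19, power 58%.
- 40% v 25%, 78 v 78 (loss of sample, no selection): (0.15 − 1.96 × 0.0750)/0.0740 = 0.04, power 52%.
- *a* = 4: (0.1221 − 1.96 × 0.0741)/0.0735 = −0.32, power 38%.
- *a* = 8: (0.0915 − 1.96 × 0.0731)/0.0727 = −0.71, power 24%.
- *a* = 12: (0.0577 − 1.96 × 0.0718)/0.0717 = −1.16, power 12%.

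The same calculation over all randomised gives 36%, 23% and 12%.

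**When would the worse arm stop looking worse?** Set (36 − *a*)/(90 − *a*) = 0.25. Then 36 − *a* = 22.5 − 0.25*a*, so *a* = 13.5/0.75 = 18. Half of the affected patients, or 20% of the arm, would have to leave because of the effect.

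**With the fix.** Counting each patient once as ever affected, over all 90, gives 36/90 = 40% for every *a*, provided the effect that led to withdrawal was recorded.

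**The case against.** The strongest reply is that the plan is being read too closely. Four stronger readings are tempting, and the document supports none of them.

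- **The comparison is restricted to patients still attending.** The text names no denominator. This objection stands, but it does not rescue the plan, because late counts fall under either denominator.
- **The test is run separately at each evaluation.** Only the counting sentence mentions evaluation times; the chi-square sentence does not. A test on totals is possible and would keep every event recorded before a patient left. It would still miss effects that led to withdrawal between evaluations, unless they were captured at withdrawal.
- **The arm losing most patients will look safer.** In the illustration escitalopram still looks worse than tDCS in every case (37%, 34% or 31% v 25%). What happens is that a real difference shrinks, and only at later evaluations.
- **Tolerability is the basis for the 50% retention fraction.** The Design and sample size determination section bases that fraction on a published proposal for generalized anxiety disorder and the methodological similarity of that condition to depression. Tolerability enters through the claim of clinical impact only.

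It can also be said that safety tables belong in the full protocol or analysis plan, and that the questionnaire schedule is in a table not shown. Sessions are frequent up to week 10, and withdrawal assessments may exist. That is fair and limits how firmly the point can be put. Still, the article does not merely leave the method open. It states one, and the one stated is weaker than a per-patient cumulative comparison.

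**Conclusion.** The point holds as a modest and inexpensive improvement to a stated method. Counting events by evaluation, with no denominator and no cumulative per-patient measure, can understate harm at later evaluations in whichever arm loses more patients to adverse effects.

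How large this would be in the trial is unknown. It needs unequal loss due to adverse effects, and attrition is not given by arm or reason. Under the assumed rates, a 15-point excess becomes about 12, 9 or 6 points among those present. The 12% power is the extreme case, in which every escitalopram loss and no tDCS loss is due to the effect. A reader might set it against the 58% at full sample and blame selection for the whole fall, but loss of sample alone takes power to about 52%. The fair comparison is therefore 52% with 38%, 24% or 12%. Events recorded at an evaluation before departure are still counted there. The primary non-inferiority test is not affected.

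**What to change.** Make the main adverse-effect comparison the proportion of randomised (treated) patients with each effect at any post-baseline evaluation, including any effect recorded at withdrawal, with all such patients in the denominator. Report the number withdrawn because of adverse effects in each arm. Keep the per-evaluation counts as description. Counting each patient once also gives the chi-square test a clear unit.

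The cost is a change of analysis wording and, if it is not already scheduled, use of the same questionnaires when a patient withdraws. The sample size and the primary test do not change. The small downside is that a cumulative proportion does not show timing, which the per-evaluation table still gives.
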